### Sample size

We will test for an effect size of 0.32 on the PHQ-9 when comparing acupuncture and counseling (1:1) with 90% power and 5% significance, which will require 204 per group. We will test for an effect size of 0.39 when comparing either acupuncture or counseling to usual care alone (2:1), with the usual care group being half the size of the acupuncture and counseling groups, for which we will need 103 patients in the usual care group. Allowing for 20% attrition, and randomizing in the proportions 2:2:1 for acupuncture, counseling, and usual care, respectively, the total sample size required is 640 (that is, groups of 256, 256, and 128, respectively).

One hundred purposively selected patients will be invited to participate in-depth interviews using a topic guide, the number to be decided when saturation has been reached. Forty percent of them (that is, 40 participants) will be drawn from the group allocated to acupuncture, another 40% from those allocated to counseling, and 20% (that is, 20 participants) will be from those allocated to usual care alone. In order to capture and map the diversity, a sampling frame will be used with sampling criteria based on sex and baseline scores. In addition, up to 65 therapists/GPs will be recruited to take part in a qualitative sub-study, which will explore their experiences of delivering the trial intervention to patients with depression.

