### Analysis

We will compare three clinical outcomes: (1) acupuncture plus usual care *versus* usual care alone; (2) counseling plus usual care *versus* usual care alone; and (3) acupuncture plus usual care *versus* counseling plus usual care.

A pre-specified statistics analysis plan will be used. Analysis will be on an intention-to-treat basis. We will use analysis of covariance at 3 months and the ‘area under the curve’ method at 12 months to assess whether clinical differences, if any, are significant. In a secondary analysis, when comparing acupuncture with counseling ((3) above), and to better understand the treatment effect, we will control for treatment time (number and length of sessions) and empathy (patient’s score of their practitioner’s empathy) by including them as covariates in the analysis. Methods to deal with potentially missing data will be addressed in detail in the analysis plan. The proportion of missing data will be summarized at each time point by allocated treatment, and known reasons for missing data will be summarized. Multiple imputation based on the standard best-subset regression method will be used for missing data. We will also estimate whether prior expectations or preferences are effect modifiers
[26].

We will explore practitioner effects by putting a group of acupuncture patients and a matching number of controls in the same cluster and use a single summary statistic, difference between acupuncture and control means, for that cluster. We will then estimate the mean difference across clusters using the t method for the confidence interval and to test the null hypothesis that the mean difference is zero. This will deal with the problem that between cluster variability is expected to be present for acupuncture patients but not for controls. It will provide an estimate of the variation between practitioners in treatment effect as well as an estimate of the treatment effect which allows for practitioner variation.

For the qualitative data, we will audiotape the interviews (with the permission of participants) and subsequently transcribe verbatim. Qualitative data will be coded and analyzed thematically within the framework of illness narratives
[27,28] and thematic analysis
[29]. This will assist in the interpretation of the quantitative data from the trial, and provide a better understanding about who is likely to be attracted to and/or benefit from prescribed medication, from acupuncture, and from counseling.

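### Practitioner variation is allowed for only in an exploratory acupuncture-versus-control analysis; the 3-month ANCOVA and the stated 90% power treat patients as independent

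*Protocol article*

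**What the plan says.** Three parts of the protocol article bear on this.

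- **Sample size.** Acupuncture versus counseling is sized for a standardised effect of 0.32, "with 90% power and 5% significance, which will require 204 per group". Each active arm versus usual care is sized for 0.39 at 2:1, "for which we will need 103 patients in the usual care group". With 20% attrition and 2:2:1 allocation the total is 640. No ICC, caseload or design effect is mentioned.
- **Analysis, main test.** "We will use analysis of covariance at 3 months" is the stated method for judging significance at the primary time-point. No practitioner term is described.
- **Analysis, practitioner effects.** Acupuncture patients and controls are to be grouped into clusters, each cluster reduced to a difference in means, and those differences analysed with a t-based interval and test. The reason given is that "between cluster variability is expected to be present for acupuncture patients but not for controls". The article says that this analysis deals with the problem and yields an effect estimate allowing for practitioner variation. It is introduced as a way to explore practitioner effects, and only acupuncture versus control is described.

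The Interventions section shows that counseling is also delivered by individual practitioners. The Discussion reports 755 recruited and an analysis starting in September.

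**The concern.** The article recognises a dependence between patients of the same acupuncturist, but the test that decides significance, as described, does not allow for it. If outcomes of patients who share a therapist are positively correlated, an ANCOVA that treats patients as independent gives standard errors that are too small. Intervals are then too narrow, and the null hypothesis is rejected too often.

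The exploratory analysis addresses this for one of the three contrasts. Counseling versus usual care, the other primary-aim contrast, has no counterpart described. Neither has acupuncture versus counseling, where both arms are therapist-delivered and the effect of clustering would be largest.

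The same independence assumption underlies the planned power. At stake are the error rate of the headline results and the meaning of the 90% figure.

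**Working it through.** **Inputs from the article.** Effects 0.32 (1:1) and 0.39 (2:1); power 90%; significance 5%, taken as two-sided because that reproduces the figures; attrition 20%; groups of 256, 256 and 128; 755 recruited.

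**Assumed, not in the article.** Practitioner ICC 0.01 to 0.05; *m* = 10 to 20 analysed patients per therapist; the same ICC in both therapist-delivered arms; 755 split as 302:302:151.

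**1. Reproduce the stated sample size with independent patients.**

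- Acupuncture versus counseling: n = 2 × (1.960 + 1.2816)² / 0.32² = 205.2 per group (stated 204). Power at 204 per group is 89.8%.
- Active arm versus usual care at 2:1: n = 1.5 × (1.960 + 1.2816)² / 0.39² = 103.6 in usual care (stated 103). Power at 204 versus 103 is 89.7%.
- Attrition: 204/0.8 = 255 and 103/0.8 = 128.75 (stated 256 and 128).

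The figures reproduce without a design effect, so they contain no allowance for clustering.

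**2. Put clustering in.** The variance of a therapist-delivered arm mean is multiplied by DE = 1 + (m − 1) × ICC. Usual care keeps DE = 1. The ratio of true to naive variance of the difference is:

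- acupuncture versus counseling: DE;
- active arm versus usual care: (DE/n + 2/n) / (1/n + 2/n) = (DE + 2)/3.

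The correct interval is √ratio times the naive width. The true error of a nominal 5% test is 2 × P(Z > 1.96/√ratio).

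| ICC, m | DE | Width ratio: v usual care / acu v couns | True type I error: v usual care / acu v couns |
|---|---|---|---|
| 0.01, 10 | 1.09 | 1.01 / 1.04 | 5.3% / 6.0% |
| 0.02, 10 | 1.18 | 1.03 / 1.09 | 5.7% / 7.1% |
| 0.05, 10 | 1.45 | 1.07 / 1.20 | 6.8% / 10.4% |
| 0.05, 20 | 1.95 | 1.15 / 1.40 | 8.8% / 16.0% |

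**3. Power of a test that does allow for clustering**, with 20% loss. Each treated arm has an effective size of n/DE. Analysed numbers are 204.8, 204.8 and 102.4 at 640, and 241.6, 241.6 and 120.8 at 755. Power is from the noncentral t with these effective sizes.

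Example (acupuncture versus counseling at 640, ICC 0.02, m = 10): 204.8/1.18 = 173.6; SE = √(2/173.6) = 0.107; 0.32/0.107 = 2.98; power is about 84%.

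| ICC, m | At 640: v usual care / acu v couns | At 755: v usual care / acu v couns |
|---|---|---|
| 0.01, 10 | 89% / 87% | 93% / 92% |
| 0.02, 10 | 88% / 84% | 92% / 90% |
| 0.05, 10 | 85% / 76% | 90% / 83% |
| 0.05, 20 | 80% / 64% | 86% / 71% |

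Without clustering, power at 755 is about 94% for both contrasts.

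**4. Baseline adjustment.** None of these figures credits it. With an assumed baseline correlation of 0.5, and the ICC unchanged by adjustment, power for acupuncture versus counseling at 640 with ICC 0.02 and m = 10 rises from 84% to about 93%. The residual variance shrinks, but the ratio in step 2 does not, so the interval stays too narrow by the same factor.

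**The case against.** The article does not overlook practitioner variation. A reader who sees only the clause about expected variability might infer a contradiction left unaddressed. The sentence in fact opens by saying that the planned cluster-level analysis deals with the problem, and that analysis gives a valid kind of interval and test for one of the two primary-aim contrasts. This stands. What remains is the exploratory status and the restriction to one contrast.

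A reader might also infer that the plan expects clustering in both treated arms. The text names acupuncture only. Extending it to counseling is reasonable, because counseling is practitioner-delivered and the article plans to report treatment variation and measure empathy for both therapies, but it is an inference.

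A third tempting reading is that the trial is underpowered. The documents do not support that. Recruitment reached 755, and against usual care power stays at about 90% or above in three of the four scenarios shown, even without baseline credit. The lowest figures belong to the secondary contrast at the extreme of the assumed range.

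Finally, an analysis plan is mentioned but not shown, and it may specify a therapist term. That limits the point to the ANCOVA as described. It does not remove it: the article itself assigns practitioner handling to an exploratory role for one contrast and states a power figure that depends on independence.

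**Conclusion.** The point holds in a limited form. As described, the 3-month ANCOVA makes no allowance for the practitioner variability that the article expects, and the practitioner-allowing analysis is exploratory and covers one contrast of three. For any positive ICC the naive interval is too narrow and the stated 90% power too high. That direction is certain; the size is not.

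Under the assumed ICC of 0.01 to 0.05 and 10 to 20 patients per therapist, true type I error is about 5.3 to 8.8% against usual care and 6 to 16% for acupuncture versus counseling. Power at the planned 640 is 80 to 89% and 64 to 87%; at 755 it is 86 to 93% and 71 to 92%. At low ICC and small caseloads the effect is modest.

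Extra patients and baseline adjustment can restore power, but they do not correct an interval computed under independence. The interval is therefore the part that needs action.

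**What to change.** Before the September analysis:

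- Make a partially nested model the primary 3-month analysis and take all three contrasts from it. It would contain arm, baseline PHQ-9, a random therapist effect in the acupuncture and counseling arms only, arm-specific residual variances and small-sample degrees of freedom. At minimum, pre-specify it as a key sensitivity analysis for all three contrasts.
- State how patients who never attend a session enter the model: assigned to the therapist they were referred to, or treated as single-patient clusters. Either keeps the intention-to-treat set.
- Report the estimated ICC.
- Restate the 90% power as conditional on independence, and give a range over stated ICC and caseload values at 755.

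This is a change of wording in the analysis plan. The therapists' logbooks should identify who treated whom among attenders; for non-attenders the referral would have to be traced. The price is slightly wider intervals and a less favourable power statement. No results have been seen, since the article reports no interim analyses.

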## Discussion

An initial version of this protocol was approved by York NHS Research Ethics Committee (Ref no: 09/H1311/75) on 1 October 2009. A series of six protocol amendments were subsequently approved, the final one on 4 January 2012. In total, 755 patients have been recruited to the trial over an 18-month period between November 2009 and April 2011, see Figure 
1. The last of the 100 patients will be recruited to the qualitative sub-study by June 2012. Data collection will be completed by the end of June 2012. Data entry will be completed by the end of August. No interim analyses have been conducted. Analysis of clinical and health economic data will start in September and is expected to be complete by the end of 2012, followed by submission of primary results to a peer-reviewed journal in 2013.

**Figure 1 F1:**
[figure not shown]
**Recruitment of participants into the ACUDep trial (Acupuncture, Counseling and Usual GP Care for Depression).** Total number of participants recruited = 755.

## Trial status

Closed as of June 2012.
